## Statistical analysis plan

### Implementation outcomes

#### Proximal implementation outcomes

##### Facilitation workshop satisfaction and acceptability

Our analysis will address two key questions: (1) participant satisfaction with the mode and delivery of the facilitation workshop and (2) the perceived acceptability of the workshop. To assess these outcomes, we will summarize participant ratings on a five-point Likert scale (1 = strongly disagree, 2 = disagree, 3 = neutral, 4 = agree, 5 = strongly agree) using descriptive statistics (see Supplementary File 1). Open-ended survey responses will be analyzed using a thematic coding approach to identify key qualitative insights [31]. All responses will be systematically reviewed, and themes will be derived inductively by identifying and labeling meaningful units of text relevant to the research objectives.

##### Knowledge, attitude, and practices change

We hypothesize that participants' knowledge, attitude, and practices regarding the use of facilitation and order set modifications to improve antibiotic prescribing guideline adherence will improve from pre- to post-workshop training. First, to assess the reliability of the scale and subscale scores, we will use Cronbach’s alpha. Descriptive statistics and weighted means will be applied to compare participants’ reactions and learning outcomes pre- and post-workshop using Hedges and Olkin’s method [32]. Paired-sample t-tests will be conducted for each session to evaluate statistically significant differences between (suitably normalized) retrospective pretest and posttest scores.

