**Methods:**

The current study expands the strategy to a diverse set of hospitals caring for children in the US. Antimicrobial stewardship teams and surgeons from any hospital providing pediatric surgical care will be eligible to participate in facilitation training either as a single session webinar or as asynchronous modules. Based on the integrated Promoting Action on Research Implementation in Health Services (iPARiHS), the facilitation training includes didactic presentations and activities that focus on current evidence related to surgical prophylaxis, evaluation of context, interpersonal relationships, and structured processes to foster change. We will use a quasi-experimental time-series design collecting data from clinicians using a structured interview guide every six months on implementation of prophylaxis guideline congruent order sets as the primary implementation outcome. We will also evaluate trends in at least 20 hospitals collecting quality improvement data through the National Surgical Quality Improvement Program-Pediatrics (NSQIP-P) on postoperative antibiotic use, surgical site infections, and *Clostridioides difficile* infections from 2022–2027.

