### Facilitation workshop

#### Workshop updates and adaptation

In the first six months of the study, we will refine and consolidate our baseline order set and facilitation workshop to enhance scalability and accessibility. Participant feedback from our Operatic 1.0 trial has identified key improvements, including more team-based discussions, additional materials, reduced time commitment, and alignment with the latest evidence on de-implementation, facilitation, and surgical prophylaxis. To improve feasibility and dissemination, we will incorporate continuing medical education (CME) credits through Nationwide Children’s Hospital’s CME department, and offer a self-paced, asynchronous format alongside the live webinar. To address concerns about the workshop’s time demands (previously eight hours over four weeks), we aim to streamline it to three hours delivered in just one session instead of four. We will pre-record didactic content and seek permission to share interactive elements, such as role-playing exercises, ensuring a balance between structured learning and collaboration.

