Participants will also learn techniques for presenting and visualizing evidence to effectively influence surgical colleagues and promote team-driven, sustainable practice improvements. The live webinar will be offered quarterly over a two-year period, training approximately 20 participants per session. An asynchronous version, including recorded content, complementary materials, and interactive activities, will be available through the Nationwide Children’s Hospital CME website for ongoing access. Completion of the training provides access to quarterly collaborative meetings and the opportunity to contribute to ongoing data collection as part of the broader study.

Similarly, we will provide an asynchronous version of the workshop that will include pre-recorded presentations, activities, and opportunities to engage with Operatic community who have also participated in the workshop.

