#### Implementation data

##### Training feedback and evaluation survey

The Kirkpatrick framework will guide our assessment, evaluating training outcomes across four levels: Reaction (participant satisfaction), Learning (knowledge, attitude, and practice change), Behavior (application of learning), and Results (overall impact on performance or outcomes) [27]. Our post-training survey will assess the first two levels: Reaction and Learning. To assess participant satisfaction (Reaction), we will include ten items adapted from a previous assessment of workshop-based practice facilitation resources [16, 28]. To measure knowledge, and practice changes (Learning), participants will respond on a 5-point Likert scale, indicating their level of agreement or disagreement with statements assessing their knowledge, attitudes, and practices, related to facilitation strategies and antibiotic prophylaxis, before and after the workshop (see Supplementary File 1). The survey instrument was developed to align with the facilitation training modules and content (see Table 2). Data will be collected from workshop participants via a survey delivered through REDCap. A retrospective post-test survey will be used to assess both training and implementation outcomes [29, 30]. Participants will complete the survey upon finishing the workshop and will be asked to retrospectively evaluate their knowledge, attitude, and practices before the workshop and how these may have changed as a result of their participation. This approach helps mitigate potential biases in self-reporting that may arise with traditional pre-survey assessments and minimizes the under- or overestimation of initial knowledge [30]. It also simplifies the evaluation process, particularly when collecting pre-survey data is challenging [29].

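### One overall learning hypothesis is tested by separate paired t-tests per session, with no stated overall test, no stated place for asynchronous trainees and no allowance for hospital teams

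*Protocol article*

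**What the plan says.** Under Knowledge, attitude, and practices change, the protocol article hypothesizes that participants' scores "will improve from pre- to post-workshop training". It plans descriptive statistics and weighted means by Hedges and Olkin's method for the pre/post comparison, and then names the significance test: "Paired-sample t-tests will be conducted for each session to evaluate statistically significant differences between" the normalized retrospective pretest and posttest scores.

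The meaning of session has to be taken from other sections. Workshop updates and adaptation aims for a workshop of "three hours delivered in just one session instead of four". Workshop content and delivery states: "The live webinar will be offered quarterly over a two-year period, training approximately 20 participants per session". The abstract's Methods paragraph describes "facilitation training either as a single session webinar or as asynchronous modules", so the asynchronous route is a second way of taking the same training.

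The Training feedback and evaluation survey section says "Participants will complete the survey upon finishing the workshop", with no exclusion by delivery mode. Study setting and participants recruits stewardship teams and surgeon champions by hospital. A random intercept for hospital is stated only for the clinical model, under Primary hypothesis.

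**The concern.** The hypothesis is about participants as a whole, but the stated test answers a different question once per webinar. If some sessions are significant and others are not, the article gives no rule for deciding whether the hypothesis is supported. Splitting the sample also discards precision that pooling would keep.

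Asynchronous trainees attend no webinar session, so a per-session test does not say where their scores go. The article presents asynchronous training as one of its contributions to dissemination science, so its learning effect should have a defined analysis.

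Finally, a paired t-test assumes that the change scores of different people are independent. Colleagues from one hospital share a setting, a stewardship programme and probably the same webinar, so their changes may be correlated. If they are, the standard error is too small.

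**Working it through.** The article gives no sample size or power for this hypothesis, so there is no stated figure to reproduce. Its only power statement concerns the clinical outcome.

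**Inputs from the article**
- Live sessions: quarterly for two years, 4 × 2 = 8.
- Trainees per live session: about 20, so 8 × 20 = 160 live trainees.
- Asynchronous trainees: number not given.
- Significance level: two-sided 5%, stated under Secondary hypotheses for the clinical outcomes and assumed to apply here.

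**Assumed inputs**
- The standardized paired difference dz (mean change divided by the SD of the change) is varied, because no target effect is stated.
- Every trainee returns a usable survey.
- Team size is three trainees per hospital, and the ICC of change scores is 0.1 to 0.3. The ICC of 0.12 under Power and sample size calculations is for the clinical outcome and cannot simply be carried over.

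**Power of one test.** Noncentral t with n − 1 degrees of freedom and noncentrality dz × √n, ignoring clustering:

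| n | dz = 0.3 | dz = 0.5 | dz = 0.8 | dz for 80% power |
|---|---|---|---|---|
| 20 (one session) | 25% | 56% | 92% | 0.66 |
| 160 (pooled) | 97% | >99% | >99% | 0.22 |

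The standard error of the mean change falls by √(160/20) = 2.83 on pooling.

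**What eight tests would show.** With the same true dz of 0.5 in every session, the expected number of significant tests is 8 × 0.564 = 4.5. The chance that all eight are significant is 0.564⁸ ≈ 1%. One real, constant effect would therefore look inconsistent across sessions.

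**Clustering.** Design effect DE = 1 + (m − 1) × ICC. The true type I error of a nominal 5% test is about 2 × [1 − Φ(1.96/√DE)] (normal approximation). With m = 3:
- ICC 0.1: DE = 1 + 2 × 0.1 = 1.2; type I error 7.4%.
- ICC 0.3: DE = 1 + 2 × 0.3 = 1.6; type I error 12.1%.

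Over a wider assumed range (teams of two to five, ICC 0.05 to 0.30) the error runs from about 6% to 19%.

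**After pooling with clustering handled.** For 160 live trainees in teams of three, the effective n is 160/1.2 = 133 to 160/1.6 = 100. The dz for 80% power becomes about 0.22 × √1.2 = 0.24 to 0.22 × √1.6 = 0.28, still far below 0.66. Asynchronous trainees would add to this.

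**The case against.** **An overall estimate may already be planned.** The sentence before the t-tests plans weighted means by Hedges and Olkin's method, which may well pool the sessions. This stands. A reader might infer that the trial cannot give any overall estimate of learning gain, and the text does not support that. What remains is narrower: no overall test is named, and the article does not say what the weights combine.

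**Session could mean a content block.** The survey was built to align with the training modules, and Table 2 lists six. On that reading each test could pool all respondents, and the figures for eight tests of 20 would not apply. The reading is possible, but the abstract, the adaptation section and the delivery section all use the word for one delivery. Even so, several tests would remain with no overall verdict.

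**Asynchronous trainees are not excluded.** This is correct: neither the survey nor the hypothesis shuts them out. A reader might infer that this route goes untested, but the article is only silent on how those trainees enter the test.

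**The error rates are conditional.** A reader might quote 1 − 0.95⁸ = 34% as the chance of a false positive. That figure needs no effect in any session and a rule that one significant session is enough, and the article states no such rule. The clustering figures rest on an assumed team size and an assumed ICC of change scores, and pairing already removes stable hospital differences in level. Low power matters only for small to moderate effects.

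**A condensed article may leave such detail to a full plan.** This covers what is left unsaid about clustering. It does not cover a test that the article does state and that fits its own hypothesis poorly.

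**Conclusion.** The point holds as a minor improvement. The stated test does not match the single hypothesis: on the better-supported reading it yields about eight tests of about 20 live trainees. Each reaches 80% power only at dz of about 0.66, against 0.22 for the pooled live sample, ignoring clustering. No rule combines the tests, and asynchronous trainees have no stated place in them.

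Treating colleagues from one hospital as independent would raise a nominal 5% error to about 7% to 12% if teams of three and an ICC of 0.1 to 0.3 are realistic; the article gives neither figure for survey scores. The outcome is a proximal implementation measure, so the primary clinical analysis and its power calculation are not touched.

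**What to change.** Make the main analysis one pooled model of each participant's posttest minus retrospective pretest score, over all live and asynchronous trainees. Handle hospital clustering with a hospital random intercept or hospital-cluster-robust standard errors, and include a fixed effect for delivery mode. Report the overall mean change with a 95% confidence interval and the change by mode. Show per-session results descriptively only, define session, and state what the weighted means pool.

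Do not add a random intercept for the webinar offering: asynchronous trainees have no offering, and hospital teams are largely nested within offerings.

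The cost is a change of wording and one model on data already being collected. Where clustering is present, intervals will be somewhat wider than in a pooled analysis that ignores it: by √1.2 = 1.10 to √1.6 = 1.26 under the assumptions above. The change is worth making under either reading of session.

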#### Distal implementation outcomes (order set changes)

We will also analyze distal implementation outcome measures descriptively, using these results to inform analyses of clinical outcomes. In our Operatic 1.0 study, we encouraged participants to target surgical procedures that they felt were modifiable, and, as a result, different ASPs targeted different procedures in their respective hospitals. We will descriptively analyze these results to understand which procedures are successfully targeted for order set changes and which facilitation skills are being used over time. This information will guide our clinical analyses to understand what surgical specialties and/or specific procedures are likely to have been most impacted (e.g., spine procedures). As appropriate, we will fit general linear models to evaluate change in our implementation outcomes before and after the workshop long term.

### Clinical outcomes

#### Primary hypothesis

We hypothesize that the appropriately lagged post-intervention percentage of cases receiving unnecessary postoperative antibiotic prophylaxis will be significantly lower than in the pre-intervention period. To test this hypothesis, we will use an intention-to-treat approach for the primary analysis, including all complete case patient data from the NSQIP-P analysis set. A mixed-effects logistic interrupted time series (ITS) regression model will assess the impact of "order set change resulting in reduction" (1) versus "no order set change" (0) on prophylaxis prescriptions. The model will include the intervention (pre vs. post), time (in months), and an interaction term between time and intervention, including a random intercept to account for intra-hospital correlation in the model. The post-intervention slope (β_2) will be the primary estimate of interest (Fig. 2), but we will also investigate differences at 12, 24 and 36 months. The interruption point will be 12 months after each hospital’s first training, with sensitivity analyses at lags 9, 15, and 18 months as well. We will extend the model to adjust for age, surgical subspecialty, procedure type, hospitalization duration, and co-morbidities using Akaike information criterion (AIC)-based variable selection. Subgroup analyses by procedure type and hospital will also be conducted.

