## Methods

### Study design

This study will use a quasi-experimental design with an interrupted time-series analysis to compare three years pre (2022–2024) and post (2025–2027) intervention. The intervention will involve training ASP teams and surgeons in facilitation strategies in addition to conducting order set review and modification. We hypothesize that a combined order set and facilitation training will result in a significant reduction in excessive post operative prophylaxis use, by fostering better engagement between ASP teams and surgeons, such as helping negotiate different communication styles and understanding of relevant data presentation. The primary endpoint of the study is the percentage of inappropriate antibiotic use. Secondary endpoints will investigate change in SSI and CDI rates.

The Nationwide Children’s Hospital Institutional Review Board (IRB) has deemed this study non-human subjects research (IRB #: STUDY00004505). An information sheet will be provided to adult ASP team members and surgeons completing the surveys. The Standard Protocol Items: Recommendations for Interventional Trials (SPIRIT) Checklist guided the development of this protocol manuscript [19].

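### The primary model is given two incompatible exposures under one intention-to-treat label: order set change (1/0), and period dated from training

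*Protocol article*

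**What the plan says.** All of the following is in the protocol article. Under Primary hypothesis the analysis is introduced thus: "we will use an intention-to-treat approach for the primary analysis, including all complete case patient data from the NSQIP-P analysis set". The next sentence says that the mixed-effects logistic interrupted time-series model "will assess the impact of 'order set change resulting in reduction' (1) versus 'no order set change' (0) on prophylaxis prescriptions".

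The rest of that paragraph describes something else. The hypothesis is that the lagged "post-intervention percentage of cases receiving unnecessary postoperative antibiotic prophylaxis will be significantly lower than in the pre-intervention period". The model terms are listed: "The model will include the intervention (pre vs. post), time (in months), and an interaction term between time and intervention". The break is dated by training: "The interruption point will be 12 months after each hospital’s first training, with sensitivity analyses at lags 9, 15, and 18 months as well". An order set indicator appears neither among the listed terms nor among the adjustment covariates.

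Under Study design, order set work is part of the intervention itself: "The intervention will involve training ASP teams and surgeons in facilitation strategies in addition to conducting order set review and modification". Yet order set change is also an outcome. The Abstract makes guideline-congruent order sets the primary implementation outcome. The logic model text, Data collection, and Distal implementation outcomes all class order set change as distal. Order sets review says that it is ascertained by short structured interviews at about 6, 12 and 18 months after the workshop.

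**The concern.** For a training programme, intention-to-treat means that every trained hospital and every eligible case after the training date (plus lag) counts as exposed, whatever the hospital then does. An indicator for having made a duration-reducing order set change is set by what happened after training. A model using it as exposure compares sites where the strategy worked with sites where it did not.

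Two things are at stake. First, the question changes. The stated goal is to disseminate the workshop and learn what that achieves; the order set contrast asks what happens where an order set was reduced. Second, the order set contrast is open to selection. Distal implementation outcomes reports that teams in the earlier trial were encouraged to pick procedures they thought could be changed, so change may follow receptiveness or a decline already under way. While both definitions stand, the choice of primary exposure could also be made after results are known.

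**Working it through.** The plan gives no figure on this point, so there is none to reproduce. The main check sets the two definitions side by side.

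| | Order set coding | Training-date coding |
|---|---|---|
| Value set by | Change reported after training | First training + 12 months |
| Trained hospital, no change | 0 | Post |
| Order set modified, duration unchanged (a possible interview answer) | Neither 1 nor 0 | Post |
| First change after the last interview (18 months); clinical data run for three years | Not captured | Post |
| Respondent lost, no alternative found | Undefined | Post |
| Unit (hospital, procedure or period) | Not stated | Hospital by month |
| Fits the intention-to-treat label | No | Yes |
| Fits the hypothesis and listed terms | No | Yes |

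**Difference in estimand.** Suppose a share s of cases falls under a reduced order set, the effect there is d, and there is no effect elsewhere. The training-date effect is then s × d. With d = 5 points (the target under Power and sample size calculations, read as percentage points) and s assumed at 80%, 60% or 40%, it is 0.8 × 5 = 4, 0.6 × 5 = 3 or 0.4 × 5 = 2 points. The article gives no value for s.

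**Selection, as an illustration only.**
- From the article: 20 hospitals, 14 cases per hospital per month, 45% baseline, ICC 0.12. On the log-odds scale the ICC gives a between-hospital SD of √(0.12/0.88 × π²/3) = 0.67.
- Assumed: 36 months before and 24 after the break (504 and 336 cases per hospital), half the hospitals change an order set, hospital-specific drift centred on zero with SD 0.2 or 0.4 log-odds, and correlation ρ between changing and favourable drift.
- Model: logit(p_pre) = a; logit(p_post) = a + drift + effect × changer.
- Contrasts: mean post minus pre over all hospitals (training-date coding), and the same change in changers minus non-changers (order set coding). Each setting used 2,000 draws.
- Effect where present: log[(0.40/0.60)/(0.45/0.55)] = −0.205, in changers only.

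| Setting | Training-date contrast (points) | Order set contrast at ρ = 0 / 0.3 / 0.6 (points) |
|---|---|---|
| No effect, drift SD 0.2 | within 0.1 of 0 | 0.0 / −2.0 / −4.1 |
| No effect, drift SD 0.4 | within 0.2 of 0 | −0.1 / −4.0 / −8.1 |
| Effect in changers only, drift SD 0.2 | −2.2 | −4.6 / −6.5 / −8.6 |

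At ρ = 0 with no effect there is no spurious benefit. At ρ = 0 with an effect, the order set contrast is about twice the training-date one (4.6 against 2.2). That is the estimand difference at s = 50%, not bias. At ρ above 0, selection adds to it.

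These are changes in level without adjustment for time. The plan's primary estimate is the post-intervention slope, and its model has time terms that would absorb part of a pre-existing decline. The figures show the mechanism and do not forecast the trial's bias.

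**The case against.** The strongest reply is that one sentence is loosely worded and the rest of the paragraph is sound. The hypothesis, the listed terms and the break point all date exposure by training, and Study design, Data collection and the power section also frame the clinical comparison as pre versus post. Because order set modification is part of the intervention, the 1/0 wording may be shorthand for post versus pre. This has force: a reader might infer that an as-treated analysis has been settled on, and the article does not support that. What remains is that the sentence, followed as written, codes a different variable from the one listed, and nothing says which governs.

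A reader might also infer that observed successes will choose the primary analysis set, since Distal implementation outcomes says "This information will guide our clinical analyses to understand what surgical specialties and/or specific procedures are likely to have been most impacted". The text does not go that far. The primary set is fixed as all complete cases in the registry data, and procedure type is named separately for subgroup analysis.

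On interviews, the article plans to seek an alternative respondent where staff have left, so undefined exposure would arise only where that fails, and only under order set coding.

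**Conclusion.** The contradiction is firm: under Primary hypothesis, one intention-to-treat label covers two exposures that classify the same trained hospital differently. Only the training-date version fits the label, the hypothesis and the listed model terms.

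The consequence is conditional. If order set change is used as the exposure, the analysis is as-treated, estimates something other than the effect of disseminating the training, and can be biased. The likely direction is towards benefit, if changers are more receptive or already declining.

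A reader might infer that the effect is inflated by a known factor such as 1/s. The documents do not support that. The ratio compares two estimands and assumes that training does nothing where no order set changed, although facilitation aimed at surgeons could act without an order set edit. The share changing, the hospital drift and its correlation with changing are all absent from the article. The illustrative null contrasts of about 0 to −8 points rest wholly on assumed values for them.

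**What to change.** State one primary exposure under Primary hypothesis: period relative to each hospital's first training plus the stated lag, for all trained hospitals and all eligible cases, whether or not an order set changed. Remove the 1/0 order set coding from the primary model. Keep order set change, time-varying and by procedure, as a secondary analysis labelled as-treated or mediation.

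This takes about two sentences and no new data. The price is that the primary effect may be smaller, because it includes hospitals that changed nothing. The power section already states its 5% target as a pre/post difference, so that target would then apply to all trained hospitals.

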#### Secondary hypotheses

We will also test multiple secondary hypotheses to assess the additional impact of the implementation strategy. These include: (1) the rate of SSI does not change post-intervention and (2) the rate of CDI decreases post-intervention. Analogous ITS-type statistical models will be fitted to investigate secondary outcomes. All estimated effects will be reported as odds ratios with 95% confidence intervals and p-values. The tests will be two-sided with a 5% statistical significance level and will be conducted using R statistical software.

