#### Power and sample size calculations

The sample size calculation is based on the primary outcome of the percentage of cases in which unnecessary postoperative antibiotic prophylaxis is administered among clean and clean-contaminated cases in the 20 participating hospitals. For the purposes of the power calculation, the staggered temporal implementation of the intervention in each of the hospitals is approximated by assuming a stepped-wedge cluster randomized trial design and adopting the sample size formula and associated web-based tool of Hemming and colleagues [35]. Utilizing data from our previous clinical trial specific to spine procedures [36], this sample size calculation depends on the targeted effect size (a percentage decrease from 45% measured in the pre-intervention period), the number of steps (10, with two hospitals implementing the intervention approximately every month over a period of 12 months), the estimated number of procedures per month (14 per hospital per month), and the intra-cluster correlation (ICC) coefficient (estimated at 0.12 from previous studies) [37]. With 20 hospitals implementing the intervention over a (1 [pre-] + 1 year [training] + 3 [post] =) 5 year study period, we envisage attaining at least 80% power to detect a difference in the pre- and post-intervention outcome measure of at least 5%, with a (two-sided) statistical significance level of 5% (and no missing data). Here we assume that existing surveillance measures capture data for the pre-intervention period and make the conservative assumption that all participating hospitals have one or more years pre-intervention surveillance data (not part of the study period), and *at least* 3 years post-intervention follow-up, allowing for the 12-month lag in post-training effect.

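### The primary slope is tested with only a hospital random intercept, so its standard error leaves out any between-hospital variation in trend or effect, and type I error can exceed 5%

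*Protocol article*

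**What the plan says.** The Primary hypothesis section of the Protocol article sets out the model in full. On the fixed effects: "The model will include the intervention (pre vs. post), time (in months), and an interaction term between time and intervention". On clustering: "including a random intercept to account for intra-hospital correlation in the model". The post-intervention slope, β_2, "will be the primary estimate of interest". The break is staggered by hospital: "The interruption point will be 12 months after each hospital" first trains staff. Under Secondary hypotheses, "The tests will be two-sided with a 5% statistical significance level", and models of the same type are to be used for surgical site infection and C. difficile infection.

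No other term for hospital is stated: no random slope, hospital-specific intervention effect, hospital-by-period term or robust variance. The planned sensitivity analyses change only the lag. The extension by AIC adds case-level covariates. Hospital otherwise appears only as a subgroup.

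Two other places bear on whether hospitals behave alike. The section on distal implementation outcomes reports that in the earlier trial "different ASPs targeted different procedures in their respective hospitals". The Discussion presents the hospitals as varied in how developed and how well supported their stewardship programmes are.

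**The concern.** A random intercept lets hospitals differ in level but gives them one common trend and one common change at the break. If hospital trends or responses differ, the estimated slope depends on which 20 hospitals took part. That uncertainty shrinks with the number of hospitals, not the number of cases. The model-based standard error shrinks with cases, so the two separate as caseload grows.

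At stake are the p-value and interval for the primary estimate. Intervals would be too narrow and a null effect could be declared significant more often than one time in twenty. The secondary models would inherit the problem.

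**Working it through.** **Inputs from the Protocol article.** 20 hospitals; 10 steps of two hospitals, about one a month; baseline 45%; 14 cases per hospital-month; ICC 0.12 (all Power and sample size calculations). Two-sided 5% test (Secondary hypotheses). Data 2022–2027, 72 months (Study design). Up to 1,500 registry cases a year per hospital, 1,500/12 = 125 a month (Clinical data).

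**Assumed, because not given.** The SD of hospital trends: 0.05, 0.1 and 0.2 logit per year. Near 45%, one logit unit is 0.45 × 0.55 = 0.2475 in probability, so these are about 1.2, 2.5 and 5.0 percentage points a year.

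**Layouts (months to the first break / total).** 48/72: training from the start of 2025 plus the 12-month lag, within 2022–2027. 12/60: a reading of the five-year period in the power section. 48/96: at least three years after every break.

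**The plan's own figures.** The stated power of at least 80% is for a pre/post difference, where the staggered rollout "is approximated by assuming a stepped-wedge cluster randomized trial design". A stepped-wedge calculation with constant within-hospital correlation gives 60% for 60 monthly categorical periods and 98% with linear time. The figure therefore depends on a period structure that is not given, and it does not address the slope. The figure that matters here is the nominal 5%. When the stated model is correct, simulation returns 5% for the slope change and 5–6% for the post slope.

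**Simulation, no average effect.** Intercept SD = √[0.12/0.88 × π²/3] = 0.67 logit. The stated fixed effects were fitted with hospital intercepts as fixed, a close stand-in for a random intercept at 840 or more cases per hospital (14 × 60). There were 1,000 runs per scenario (Monte Carlo SE about 0.7 points at 5%). The text lists an interaction, while the Fig. 2 caption calls β_2 the post-intervention trend, so both readings are shown.

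| Hospital-trend SD (logit/yr) | Layout | Slope change | Total post slope |
|---|---|---|---|
| 0.05 | 48/72 | 6.0% | 5.9% |
| 0.05 | 12/60 | 5.3% | 8.9% |
| 0.05 | 48/96 | 6.3% | 10.7% |
| 0.1 | 48/72 | 9.2% | 9.8% |
| 0.1 | 12/60 | 8.7% | 23.3% |
| 0.1 | 48/96 | 12.1% | 25.0% |
| 0.2 | 48/72 | 20.2% | 21.6% |
| 0.2 | 12/60 | 18.7% | 46.6% |
| 0.2 | 48/96 | 27.8% | 48.5% |

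**Check by approximation.** True SE = √(model SE² + added SE²), and type I error = 2[1 − Φ(1.96 × model SE / true SE)]. For the slope change in layout 48/72 the model SE is 0.0565. A trend SD of 0.1 adds 0.0373, so the true SE is √(0.0565² + 0.0373²) = 0.0677 and the error is 2[1 − Φ(1.64)] = 10%. For the post slope in layout 48/96, √(0.0172² + 0.0243²) = 0.0298, giving 26%. The added 0.0243 is close to 0.1/√20 = 0.0224, the SE of an average of 20 hospital trends. With about 54 months after the break, the post-slope error reaches 13%, 30% and 56% at the three SDs.

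**Other sources of variation, 14 cases a month (slope change / post slope).**
- Slope changes varying by hospital, SD 0.1: 6–19% / 7–24%. SD 0.2: 12–37% / 14–47%.
- Independent hospital-month noise: 6–7% / 5–6%.
- Shared autocorrelated calendar shock, SD 0.05: 10–17% / 11–18%.

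**Larger caseload.** At 100 cases a month (layouts 48/72 and 48/96), trend SD 0.1 gives 32–37% / 38–55%.

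**Effect of the remedy.** Cluster-robust SEs with t on 19 df bring the error to about 4–7% under hospital-level variation. Under shared calendar shocks (SD 0.05–0.1) rejection stays at 9–38%.

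**Price of calendar terms.** Replacing linear time by calendar quarters raises the slope-change SE from 0.057 to 0.133 (48/72), 0.071 to 0.134 (12/60) and 0.022 to 0.098 (48/96), which is 1.9 to 4.5 times.

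**The case against.** The strongest reply is that the protocol gives no variance for hospital trends, and that at the low end little happens: with SD 0.05 the slope-change test is essentially sound. This stands. A reader might infer that intervals are bound to be too narrow and the error rate well above 5%; the documents do not support that.

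Nor do they show that trends must differ. The remark on different target procedures describes what teams chose in the earlier trial, not background trends, and if training did nothing anywhere, different targets would create no differing effects. It makes variation in effect plausible; the Discussion's account of varied hospitals does the same for trends.

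Stable hospital trends might be expected to cancel from the slope change. In the linearised model they do when every hospital breaks in the same month. With staggered breaks they do not cancel fully, as the slope-change column shows. Inflation in the level change is not the point here, since the primary estimate is a slope.

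A reader might also want calendar terms in the primary model because training is staggered. If time in months is calendar time, a linear secular trend is already adjusted for. With hospital intercepts as fixed effects, linear calendar time and linear time since training are collinear, so only non-linear terms add anything. After a 10-month rollout no untreated hospital remains, and the loss of precision is severe.

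Finally, degrees of freedom and seasonality are often left to an analysis plan, and one may exist. But the protocol names the random intercept as its means of handling intra-hospital correlation, so that choice can be judged.

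**Conclusion.** The point holds in conditional form. The stated model gives no protection against between-hospital variation in trend or effect, no stated supporting analysis corrects the standard error, and the document makes such variation plausible. Intervals are likely too narrow and type I error can exceed 5%. At 14 cases a month the excess is negligible to modest at an assumed trend SD of 0.05 logit per year, clear at 0.1 and large at 0.2. It is greater for the total post slope than for the slope change, and greater with the full registry caseload. All variances are assumptions, and the layout matters because the documents allow several. Shared calendar shocks are a further risk that hospital-level remedies do not remove.

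**What to change.** Before analysis, amend the primary model to include hospital-level random effects for time and for both intervention terms (level and slope change), and/or base inference on small-sample-corrected cluster-robust standard errors with t on about 19 df. Keep the random-intercept model as a sensitivity analysis. Apply the same change to the surgical site infection and C. difficile models. State whether β_2 is the interaction or the total post-intervention slope, since the size of the problem differs.

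Add flexible calendar-time terms, such as calendar quarter, as a sensitivity analysis only, with a note that they raise the slope-change SE several-fold under the planned rollout.

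No new data are needed. The cost is wider intervals: about 7% from the t reference alone (2.093/1.96), and about 28% for the slope change in layout 48/72 at trend SD 0.1 (0.0677/0.0565 × 2.093/1.96). Random slopes may also be hard to estimate with 20 hospitals, in which case the cluster-robust route is the simpler one.
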